### Analysis

#### Feasibility and acceptability

Data from screening logs completed by each centre will provide information on the participant screening process and will be analyzed descriptively. Reasons for non-entry into the trial will also be assessed, particularly in relation to the patient eligibility criteria and reasons for patient refusal.

Data on patients who do not complete the trial (such as withdrawals and those lost to follow-up) will also be collected throughout the trial to allow assessment of patient retention rates and reasons for non-completion of the trial. Reasons for non-completion will be analyzed descriptively.

#### Adherence to SLT interventions

LSVT® is an intensive course of treatment. In this group therapists will provide information on the mean number and duration of sessions each patient receives during the study in order to assess patient and therapist compliance with LSVT®. Patients will also be asked to document SLT homework in diaries.

Therapists administering standard NHS SLT will also be logging information on the SLT sessions providing information on number and duration of sessions and the type of therapy provided. This will give some insight into the content and fidelity of standard NHS SLT, with the mean number and duration of sessions presented, along with a descriptive analysis of the SLT content.

#### Outcome data

Data from this pilot study will also be used to inform the choice of outcome measures, provide data to inform a sample size calculation, and pilot the health economic evaluation for the full-scale trial.

Data return rates at each time point will be assessed along with data completeness of the various outcomes measures. The outcome data collected will be summarized using descriptive statistics and an exploratory analysis will be performed. Analyses will be performed using intention-to-treat. Data at each time point for each arm will be presented as means with standard deviations. The differences between the arms (LSVT® versus no intervention, NHS SLT versus no intervention, and LSVT® versus standard NHS SLT) in the means and mean change from baseline to 3, 6, and 12 months will be calculated, along with the 95% confidence intervals. This will help to determine the sensitivity of the outcome measures to change. Appropriate techniques (such as correlation methods) will be used to identify which outcome measures are closely related, which will then inform which outcome measures to take forward for use in a full-scale phase III trial. The data collected within this pilot study (estimate of the variability and treatment effect size) will help inform a sample size calculation for a full-scale trial.

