### Recruitment

Recruitment will take place from 11 neurology and elderly care NHS clinics from a mix of urban and rural areas in the UK. The UKCRN networks will be asked to adopt the study to support recruitment. Informed consent will be obtained for all participants recruited into the study.

For a feasibility study no formal sample size calculation is required. We aim to recruit at least 60 participants over 21 months from the 11 sites (at least 20 participants in each arm of the trial) which will provide enough data to inform a future phase III trial
[16].

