### Consent and randomization

Potential participants who meet the eligibility criteria will be initially approached in their normal outpatient appointments. If interested, they will be given a patient information sheet and time to consider the trial and discuss it with friends and family. A further meeting will be arranged to answer any questions prior to informed consent being taken. Following consent, participants will complete baseline assessments prior to randomization. Participants will be informed of their treatment allocation and, if allocated therapy, be referred for the initial assessment. Baseline vocal assessments may be performed after randomization but must be completed prior to the start of therapy.After completing the baseline questionnaires, participants will be randomized between the three groups at a ratio of 1:1:1 via the Birmingham Clinical Trials Unit (BCTU) telephone randomization service (Figure 
1). This secure central randomization service is available between 9 am and 5 pm weekdays and will ensure the concealment of treatment allocation. A computer-generated randomization list will be used. Participants will be informed of their treatment allocation but assessors will remain blind to treatment allocation. If allocated to an intervention arm, referral to the appropriate speech and language therapist will occur immediately following randomization. All personal information obtained for the study will be held securely and treated as strictly confidential.

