### Outcome measures

Data on various outcomes measures will be collected as part of the PD COMM pilot in order to assess which outcomes are appropriate to take forward to the phase III RCT. These include both participant, therapist, and carer completed questionnaires and measures. Outcome measures will be assessed at baseline (pre-treatment), 3 months (post-randomization - to allow for any delays in referral to therapy and the varying intervention lengths), 6 months, and 12 months post-randomization (to see if any benefit is maintained). Assessment will take place at the therapy departments of participating centers and will be conducted when the participant is ‘on’ medication (if medicated). Vocal assessment of intelligibility of dysarthric speech (AIDS), loudness, and comprehension will be recorded and assessed by assessors masked to the participant’s group allocation. Participant completed questionnaires will be conducted via post.

Effectiveness of communication will be measured using the self-report Voice Handicap Index (VHI)
[23]. The VHI has previously been used as an outcome measure in an extended LSVT® trial for PD
[20]. Intelligibility will be assessed using AIDS
[24]. Participants will be digitally recorded speaking randomly generated words and sentences from AIDS. These will then be transcribed by three blinded assessors. Vocal loudness will be measured through sound pressure level (in decibels) for a sustained vowel (’ah’) phonation, the reading of a ‘rainbow passage” (an articulation exercise including all the normal sounds of spoken English), and speaking freely during a self-chosen monologue
[18]. These will be audio-recorded and assessed by a blinded assessor. A comprehensibility assessment will be made using a picture, the ‘cookie theft’ picture from the Boston diagnostic aphasia examination
[25]. This will be digitally recorded and assessed by three blinded assessors. Quality of life (QoL) will be recorded through two self-report measures; the PD-specific 39 point Parkinson’s Disease Questionnaire (PDQ-39
[26] and the voice specific Voice-Related QoL scale (V-RQOL)
[27]. Participation restriction related to speech and communication will be assessed using the self-report Living with Dysarthria questionnaire (LwD)
[28]. The effect on carers will be measured through the self-report Parkinson’s Carers’ Quality of Life Questionnaire

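### Between-arm estimates are planned only as unadjusted differences in means and in change; adding a baseline-adjusted estimate would usually be more precise and would correct for chance baseline imbalance in arms of about 20

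*Protocol article*

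**What the plan says.** The Outcome data section says the outcomes will be "summarized using descriptive statistics and an exploratory analysis will be performed". It then specifies the summaries: "Data at each time point for each arm will be presented as means with standard deviations". For the three pairwise contrasts (LSVT against control, NHS SLT against control, LSVT against NHS SLT) it plans differences "in the means and mean change from baseline to 3, 6, and 12 months will be calculated, along with the 95% confidence intervals". No model with the baseline score as a covariate is mentioned.

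The section gives these results two uses. They are to show how sensitive the measures are to change, and the data are to feed phase III planning: "estimate of the variability and treatment effect size) will help inform a sample size calculation for a full-scale trial".

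Table 1 shows a baseline for all ten outcome scales: AIDS, vocal loudness, comprehensibility, VHI, PDQ-39, V-RQOL, LwD, EQ-5D, ICECAP-O and the carer questionnaire. Only the resource-use questionnaire lacks one. The three vocal measures have no 12-month visit. The Recruitment section sets the size as "at least 20 participants in each arm of the trial", and Consent and randomization says participants are "randomized between the three groups at a ratio of 1:1:1". That section also lets vocal baselines be recorded after randomization, provided therapy has not begun.

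**The concern.** A difference in follow-up means makes no use of the baseline. A difference in mean change subtracts the whole baseline difference, which is too much whenever the correlation between baseline and follow-up is below 1 (with equal SDs). If two arms differ at baseline by chance, the first estimate moves one way and the second the other, and they disagree by exactly the size of the imbalance. In arms of 20 such imbalances are common enough to matter.

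No test or efficacy claim is at stake. What is affected is the width of the intervals, how the one realised data set is read when the two estimates disagree, and the quality of the effect and variability estimates used to compare outcome measures and to plan phase III.

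**Working it through.** **Plan's own figure.** There is no power calculation to reproduce: "For a feasibility study no formal sample size calculation is required". The target is consistent: 3 × 20 = 60.

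**Inputs.** n = 20 per arm (Recruitment) and 95% intervals (Outcome data). The outcome SD is set to 1 and taken as equal at baseline and follow-up. The article gives no baseline-to-follow-up correlation, so ρ is an assumption and is shown over a range.

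**Precision.** Variance of a two-arm difference, relative to raw means:
- raw means: 1
- change scores: 2(1 − ρ)
- baseline-adjusted: (1 − ρ²) × [1 + 1/(2n − 4)] = (1 − ρ²) × 1.028. The last factor is the small-sample cost of estimating the slope.

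Half-width = t × √(2/20 × V), with 38 df for raw means and change and 37 df for the adjusted estimate. At ρ = 0.5 the adjusted V is 0.75 × 1.028 = 0.771, giving a half-width of 0.56. Raw means give 0.64.

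| ρ | V raw | V change | V adjusted | Half-width raw / change / adjusted (SD) |
|---|---|---|---|---|
| 0 | 1 | 2.00 | 1.028 | 0.64 / 0.91 / 0.65 |
| 0.1 | 1 | 1.80 | 1.017 | 0.64 / 0.86 / 0.65 |
| 0.2 | 1 | 1.60 | 0.987 | 0.64 / 0.81 / 0.64 |
| 0.3 | 1 | 1.40 | 0.935 | 0.64 / 0.76 / 0.62 |
| 0.5 | 1 | 1.00 | 0.771 | 0.64 / 0.64 / 0.56 |
| 0.7 | 1 | 0.60 | 0.524 | 0.64 / 0.50 / 0.46 |
| 0.9 | 1 | 0.20 | 0.195 | 0.64 / 0.29 / 0.28 |

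A simulation of 20,000 two-arm trials at each of ρ = 0, 0.3, 0.5, 0.7 and 0.9 agreed with the formulas. At ρ = 0.5, for example, it gave variances of 1.008, 1.000 and 0.776.

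**Chance imbalance.** The SE of a baseline difference between two arms of 20 is √(2/20) = 0.316 SD.
- P(|difference| > 0.3 SD) = 2[1 − Φ(0.3/0.316)] = 0.34 for one pair.
- P(|difference| > 0.5 SD) = 0.11 for one pair, and about 0.25 for at least one of the three pairs (simulated).

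An imbalance of size δ shifts the raw contrast by ρδ and the change contrast by (ρ − 1)δ. For δ = 0.5 SD:
- ρ = 0.3: +0.15 and −0.35 SD
- ρ = 0.5: +0.25 and −0.25 SD
- ρ = 0.7: +0.35 and −0.15 SD

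In each case the two planned estimates lie 0.5 SD apart for reasons unrelated to treatment. Adjustment removes this shift for the baseline score in the model, but not for other covariates.

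**What ρ means for phase III (illustration only).** Assume an effect of 0.5 SD, 80% power and two-sided 5%. Then n per arm = 2(1.96 + 0.84)² × V/0.25, using V without the small-sample factor. For raw / change / adjusted this gives 63 / 88 / 58 at ρ = 0.3, 63 / 63 / 48 at ρ = 0.5, and 63 / 38 / 33 at ρ = 0.7. The spread shows why ρ is worth reporting directly.

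**The case against.** This is an exploratory pilot without a power calculation, and the article's Discussion disclaims any conclusion on effectiveness. Both planned estimators are unbiased over randomization. The gain depends on an unknown ρ: against the better planned method it is small at 0.7 (0.50 to 0.46 SD), almost nil at 0.9, and slightly negative at 0 to 0.1. A 0.3 SD imbalance at ρ = 0.5 moves either contrast by only 0.15 SD, well inside a half-width of 0.64. All of this stands, and it limits the point to a modest one.

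Mean change also serves the stated aim of judging sensitivity to change. That stands too, so change scores should not be dropped.

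A reader might infer that the SD handed to phase III would be the wrong one. The article does not support this. How phase III will be analysed is not stated, and the planned output largely contains what is needed. With SDs s₀ (baseline), s₁ (follow-up) and s_c (change) on the same participants, ρ = (s₀² + s₁² − s_c²)/(2s₀s₁), and the residual SD is s₁√(1 − ρ²). With slope b, the adjusted difference is (1 − b) × raw difference + b × change difference, so apart from missing data little information is lost. Nor is it a fault that the article does not say which estimate will drive the phase III calculation, since such detail is commonly left to a fuller document.

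Pilot status does not remove the point, because the section itself uses the contrasts and their variability for choosing outcomes and for planning.

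**Conclusion.** The point holds as a low-cost improvement to a stated analysis. It does not show that the planned analysis is biased or invalid. With 20 per arm and equal SDs at baseline and follow-up, the adjusted estimate is at least as precise as both planned estimates for assumed ρ from about 0.2 to 0.9. Its variance at ρ = 0.5 is 0.77 of either. At ρ = 0.7 it is 0.52 of raw means and 0.87 of change (0.524/0.60). The advantage vanishes near ρ = 0 (against raw means) and near ρ = 1 (against change), so adjustment cannot be called more precise without condition. The shifts from chance imbalance are conditional on the realised allocation and average to zero over randomization.

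A reader might also infer that vocal outcomes should be analysed only where the baseline preceded randomization. The article does not support that: it permits later vocal baselines and commits to intention-to-treat. Change scores share any weakness that a late baseline brings.

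**What to change.** In the Outcome data section, for each outcome with a baseline and at each time point where Table 1 schedules it:

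- Add a three-arm linear model of follow-up score on arm plus baseline score. Name the three adjusted pairwise differences with 95% CIs as the main between-arm estimates.
- Keep means, SDs and mean changes as descriptive output for the sensitivity-to-change objective.
- Report the baseline-to-follow-up correlation and the residual SD for the phase III calculation.
- For vocal outcomes, keep all participants in the main model, and add a sensitivity analysis addressing those whose baseline was recorded after randomization.

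If an analysis plan that is not shown already provides this, only the wording needs to be aligned. The cost is one degree of freedom per model and 2-3% more variance than raw means if ρ is 0 to 0.1. No new data are needed.

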#### Health economics

The trial will pilot the tools to measure resource use and outcomes that may be used in a full economic evaluation alongside a larger trial. The rates of completion and sensitivity to change will be determined.

## Discussion

Speech and language therapy is an important component of treatment for people with PD. Two recent Cochrane reviews have concluded that evidence for the efficacy of SLT and different SLT techniques is lacking and therefore well-designed RCTs are needed to address this issue
[5,10]. This trial will provide important information relating to the feasibility of a definitive RCT of the effect of SLT and LSVT® in people with PD. All aspects of this trial will be scrutinized including the recruitment methods, data collection procedures, outcome measures, follow-up time points, and intervention adherence in clinical and home settings. This pilot study is a well-designed, rigorous RCT which is the largest in the field to date. It has many strengths including robust blinding and detailed approaches to the measurement and evaluation of speech, and will capture previously unconsidered information on adherence to home-based tasks. As this is a pilot trial, effectiveness will not be established. However, the data collected will be of vital importance to future clinical research and necessary to inform a phase III RCT to test the clinical and cost-effectiveness of SLT and LSVT® on speech problems in people with PD.

## Trial status

The PD COMM pilot trial is ongoing and has not completed participant recruitment which began May 2012.

## Abbreviations

AAC: Augmentative and Alternative Communication; AIDS: Assessment of intelligibility of dysarthric speech; EQ-5D: EuroQol 5 Dimensions; ICECAP-O: ICEpop CAPability measure for Older people; LSVT®: Lee Silverman Voice Treatment; LwD: Living with Dysarthria questionnaire; NHS: National Health Service; PD: Parkinson’s Disease; PDQ-39: Parkinson’s Disease Questionnaire; RCT: Randomized Controlled Trial; SLT: Speech and Language Therapy; SOPS: Standard Operating Procedures; VHI: Voice Handicap Index; V-RQOL: Voice-Related QoL scale.
